## Abstract

**Background:**

Borderline Personality Disorder (BPD) is a serious psychiatric condition associated with substantial mortality, burden and public health costs. DBT is the treatment model with the largest number of published research articles showing effectiveness. However, some patients are not sufficiently engaged in outpatient treatment while presenting severe parasuicidal behavior, making hospitalization necessary. The Center for Personality Disorders Jelgersma developed an intensive 12-week inpatient DBT program that (i) rapidly reduces core borderline symptoms like suicidal behavior, (ii) minimizes the negative effects of an inpatient setting, and (iii) enhances compliance with outpatient treatment. We evaluate the (cost-) effectiveness of this experimental program.

**Methods/design:**

Seventy patients, aged 18 to 45 years with a primary diagnosis of BPD, showing a chronic pattern of parasuicidal gestures and/or reporting high degrees of severity of other borderline symptoms, are randomly allocated to the control and intervention groups. Subjects in the control group receive standard outpatient DBT, provided in one of three regular mental health settings in GGZ Rivierduinen. Subjects in the intervention group receive 12 weeks of intensified inpatient DBT plus six months of standard DBT, provided in the Center for Personality Disorders Jelgersma. The primary outcome is the number of suicide attempts/self-harming acts. Secondary outcomes are severity of other borderline complaints, quality of life, general psychopathological symptoms and health care utilization and productivity costs. Data are gathered using a prospective, two (group: intervention and control) by five (time of measurement) repeated measures factorial design.

Participants will complete three-monthly outcome assessments in the course of therapy: at baseline, and 12, 24, 36 and 52 weeks after the start of the treatment. The period of recruitment started in March 2012 and the study will end in December 2014.

**Discussion:**

Highly suicidal outpatient patients can pose a dilemma for mental health care professionals. Although hospitalization seems inevitable under some circumstances, it has proven to be harmful in its own right. This paper outlines the background and methods of a randomized trial evaluating the possible surplus value of a short-term inpatient DBT program.

## Background

Borderline Personality Disorder (BPD) is a serious and prevalent psychiatric condition characterized by affective instability, impulsivity, and significant deficits in the capacity to work and maintain meaningful relationships. Patients with BPD struggle with a profound fear of abandonment, identity disturbances, and paranoid ideations. They are at risk for suicide and repetitive self-destructive behaviors. BPD patients show a completed suicide rate that is 50 times greater than that in the general population [1,2]. The short- to medium-term outcome of BPD is poor. There is some evidence that the long-term follow-up course is more favorable, with remission rates of about 88% within ten years [3]. However, ‘remission’ means that diagnostic criteria are not fulfilled. Affective symptoms reflecting areas of dysphoria, such as chronic feelings of emptiness, intense anger or profound abandonment, largely remain [4].

In the general population, the prevalence of BPD varies from 0.4 to 1.8%, with a pooled rate of 1.1% [5]. The lifetime prevalence of BPD was found to be 5.9% among a representative sample of the adult population of the United States [6,7]. In the Netherlands, the number of borderline patients is estimated at 100,000 [8]. In clinical samples, BPD is usually the most common personality disorder. In outpatient samples, rates of 9.3 to 18% have been reported, with a pooled rate of 11.9% [5]. Studies of psychiatric inpatient populations have reported rates of BPD at about 40% [9].

DBT is the BPD treatment model for BPD with the largest number of evidence-based published research articles on effectiveness (13 Random Controled Trials (RCT) versus 2 RCTs of next evidence treatment model off the rank). The American Psychological Association, Society of Clinical Psychology (APA) has cited DBT as one of the well-established, empirically supported, treatments for BPD that has strong research support [10]. The UK NICE guidelines recognize that, more than any other therapy, there is some evidence that DBT is effective in reducing suicide attempts and self-harm, anger, aggression and depression in patients with BPD [11]. This is also postulated in the Dutch guidelines [12].

Yet, standard DBT is lengthy and thus expensive. Moreover, some BPD patients are not sufficiently engaged in outpatient treatment and/or experience periodic exacerbations of severe self-injurious behavior making hospitalization necessary. A recent meta-analysis showed that psychotherapy for BPD yielded an overall drop-out rate of 25% [13]. Previous research also demonstrated that BPD patients are hospitalized and readmitted more than those with other disorders [14,15]. This is troublesome, since dropping out of treatment, as well as a pattern of inpatient treatments, adds to the suicide risk [16,17]. These figures frequently pose a dilemma for mental health care professionals treating highly suicidal patients in an outpatient setting. Hospitalization seems inevitable under some circumstances, yet has proven harmful in its own right. It is concluded that there is an urgent need to develop and test short-term inpatient treatment programs that (i) rapidly reduce core borderline symptoms like suicidal behavior, (ii) minimize the negative effects of an inpatient setting, and (iii) enhance compliance with outpatient treatment.

Following the publication of the SCEPTRE research results [18], and a growing number of inpatient DBT programs [19-22], the concept of inpatient treatment seems to be gaining interest. There is sufficient evidence that inpatient DBT leads to symptom reduction and that treatment gains are maintained after discharge for adult and adolescent BPD patients [23,24]. However, firm conclusions about the efficacy of inpatient DBT cannot be drawn. The effect of inpatient DBT has not been investigated in RCTs or compared to the effect of outpatient DBT. Moreover, no data on the cost-effectiveness of inpatient DBT are available.

The Center of Personality Disorders Jelgersma (GGZ Rivierduinen Leiden, Netherlands) developed an intensive 12-week inpatient DBT program that (i) rapidly reduces core borderline symptoms like suicidal behavior, (ii) minimizes negative effects of an inpatient setting, and (iii) enhances compliance with outpatient treatment. We evaluated the (cost-) effectiveness of this experimental program.

## Methods/design

### Study design

This is a prospective randomized controlled trial. It is a two (group: intervention and control) by five (time: pretreatment, 12 weeks, 24 weeks, 36 weeks, 52) repeated measures factorial design. The overall study design is illustrated in Figure 1.

**Figure 1 F1:**
[figure not shown]
**Study design.** Procedures in a study comparing experimental short-term inpatient DBT program and standard outpatient DBT.

### Participants

Participants will consist of seventy patients, aged 18 to 45 years with a primary diagnosis of Borderline Personality Disorder, according to the *Diagnostic and Statistical Manual of Mental Disorders* (DSM-IV), showing a chronic pattern of parasuicidal gestures and/or reporting high degrees of severity of other borderline symptoms. It was decided that Jelgersma Center for Personality Disorders in Oegstgeest, Regional Psychiatric Center GGZ Rijnstreek, Regional Psychiatric Center GGZ Leiden and Regional Psychiatric Center GGZ Midden-Holland, constituting all participating centers of GGZ Rivierduinen, would implement a central recruiting and diagnostic facility in order to recruit patients efficiently and uniformly. All referrals for initial assessment in this facility were considered, given that patients contact the researcher themselves and of their own free will. No restriction is made in terms of the referral source. Only hard drug abuse that requires inpatient detoxification and a forced treatment framework were refused. We predict that the majority of referrals will come from the Jelgersma Center for Personality Disorders, since this center has a nationwide reputation.

### Inclusion criteria

1) Aged between 18 and 45 years

2) Independently contacted the researcher or coached do to so

3) Fulfill the DSM-IV-TR criteria for BPD. Presence of BPD is according to semi-structured interview SCID-II, administered by a trained professional (psychologist, supervised by a project leader)

4) Show a severe level of borderline symptomatology (>24 on the Borderline Severity Index)

5) Parasuicidal behavior in the last month preceding baseline measurement and/or a profound level of borderline symptoms (>30 on the Borderline Severity Index)

6) Sufficient command of the Dutch language

7) Within travelling distance from Leiden

8) Understands and agrees with randomization procedure

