### Sample size

We expect that after 12 weeks, 20% of the patients of the intervention group will still show suicidal and/or self-harming behavior compared to 60% of the patients in the control condition. To be able to detect a difference of 40% after 12 weeks, with a power of 0.80 and an α = 0.05, a minimum of 23 patients per experimental condition is required. We will randomize between approximately 70 patients during the study period to guarantee enough power, taking into account an expected 30% drop-out rate.

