## Discussion

Mental health care professionals are frequently confronted by a dilemma when treating highly suicidal patients in an outpatient setting. Hospitalization seems inevitable under some circumstances, yet has proven harmful in its own right. This paper outlines the background and methods of a randomized trial evaluating the possible surplus value of a short-term inpatient DBT program.

Although previous quasi-experimental studies [22,23] have shown positive effects of inpatient DBT, the setting could add to the risk of regressive processes during treatment. Therefore we evaluated outcomes of the experimental short-term inpatient DBT program of the Jelgersma Center in a quasi-experimental study, comparing pre- and post-intervention data for 39 female patients with a diagnosis of BPD [54]. It was found that the severity of borderline problems, particularly in the field of interpersonal problems, was significantly reduced. In general, suicidality and parasuicidal behavior were not reduced significantly, though positive effects for patients reporting high levels of suicide attempts and self-harming behavior at baseline were found. It was concluded that the experimental program showed promise for patients who show high levels of parasuicidal behavior and that further development and research was justified. Improvements were suggested and implemented [54]. One of the most important changes made was restricting the program to patients with recent suicide attempts and severe self-harming behavior.

Four centers of GGZ Rivierduinen (Center of Personality Disorders Jelgersma, GGZ Rijnstreek, GGZ Leiden en GGZ Midden-Holland) agreed to participate in the trial. In order to rule out differences in the admittance process, an independent, central diagnostic facility was established. This resulted in an efficient, standardized intake procedure that bypasses the waiting lists in the centers. This adaption was considered to be beneficial for participants, since they know their diagnosis and the treatment program they will be part of within a few weeks.

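### Eligibility admits patients without recent parasuicidal behaviour, the Discussion says the programme was restricted to patients who have it, and the 60% vs 20% is not tied to either population

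*Protocol article*

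**What the plan says.** **Who may enter.** Criterion 5 under Inclusion criteria is "Parasuicidal behavior in the last month preceding baseline measurement and/or a profound level of borderline symptoms (>30 on the Borderline Severity Index"). Either limb suffices. The Abstract and the Participants section use the same 'and/or' construction, so this is not a slip in one place. Criterion 4 separately requires a severity index above 24 from everyone.

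**Who the programme is for.** The Discussion reports an uncontrolled pre-post study of 39 patients in the same programme: "In general, suicidality and parasuicidal behavior were not reduced significantly", although positive effects were seen in patients with high baseline levels. It then says: "One of the most important changes made was restricting the program to patients with recent suicide attempts and severe self-harming behavior".

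**What is measured and powered.** Objectives, Sample size and Statistical analysis all use the proportion still showing the behaviour at 12 weeks. The sample size assumes "20% of the patients of the intervention group will still show suicidal and/or self-harming behavior" "compared to 60% of the patients in the control condition", "with a power of 0.80 and an α = 0.05", giving 23 per arm and about 70 randomised with 30% drop-out. The analysis includes everyone randomised. The longitudinal logistic regression has time, condition and their interaction as independent variables, with no term for behaviour at entry.

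**The concern.** A patient admitted on severity alone may have had no parasuicidal behaviour in the month before baseline. Such a patient has little or nothing to stop, and counts as a good outcome in either arm unless the behaviour begins. Patients of this kind lower both arms' rates and shrink the absolute difference. If the 60% and 20% were conceived for patients who have the behaviour at entry, as 'still' suggests, the trial is planned for a larger contrast than the recruited sample can show.

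The Discussion sharpens the point. The programme was narrowed because the earlier study found no general reduction in this behaviour. The eligibility text leaves open the door that the Discussion says was closed. A reader cannot tell which population the trial recruits, or which one the assumed rates describe.

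**Working it through.** **Inputs from the protocol article (Sample size):** control 0.60, intervention 0.20, power 0.80, α 0.05 (sidedness not stated), 23 per arm, about 70 in total, 30% drop-out.

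**Step 1: the plan's own figure.** Two-sided test, pooled variance under the null, no continuity correction, mean rate 0.40:

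n = [1.96·√(2·0.40·0.60) + 0.842·√(0.60·0.40 + 0.20·0.80)]² / 0.40² = (1.358 + 0.532)² / 0.16 ≈ 22.3, so 23 per arm.

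Drop-out: 23 / 0.70 = 32.9, so 33 per arm or 66 in total. About 70 covers this. The stated figures reproduce.

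**Step 2: number analysed.** 35 per arm × 0.70 = 24.5, taken as 25.

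**Step 3: dilution model.** Let f be the share entering without the behaviour and q the proportion of them showing it at week 12 in either arm. The document gives neither, so both are assumptions. Take 60% and 20% as the rates in patients with the behaviour:

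- control rate = 0.60(1 − f) + q·f
- intervention rate = 0.20(1 − f) + q·f
- difference = 0.40(1 − f)

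With q = 0.10, exact power of the uncorrected chi-square test at 25 per arm:

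| f | Control | Intervention | Difference | Power |
|---|---|---|---|---|
| 0 | 60% | 20% | 40 points | 0.87 |
| 10% | 55% | 19% | 36 points | 0.79 |
| 20% | 50% | 18% | 32 points | 0.70 |
| 30% | 45% | 17% | 28 points | 0.60 |
| 40% | 40% | 16% | 24 points | 0.49 |

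The result is not sensitive to q. Over q from 0 to 20%, power is 0.69–0.71 at f = 20%, 0.58–0.63 at 30% and 0.46–0.54 at 40%. The normal approximation with 24 per arm and q = 0.10 gives 0.75, 0.66, 0.56 and 0.46 for f from 10% to 40%.

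**Step 4: the other reading.** If 60% and 20% are the rates in the mixed population, nothing is diluted, and power at 23 to 24 per arm is 0.81 to 0.83 by the normal approximation. The implied rates in patients with the behaviour, with q = 0, are then:

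- f = 20%: 0.60/0.80 = 75% vs 0.20/0.80 = 25%
- f = 40%: 0.60/0.60 = 100% vs 0.20/0.60 = 33%

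So with q = 0 this reading cannot hold if more than 40% enter without the behaviour. At smaller shares it is coherent.

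**The case against.** A reader might infer that the 60% vs 20% and the 80% power simply do not apply to the enrolled patients. The document does not support that. The Sample size section states the rates for the patients of each arm, without limiting them to those with the behaviour at entry, and gives no derivation. On that wording the mixed-population reading is the literal one, and the power holds. The stronger reading leans on the word 'still'.

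Other points also stand:

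- **The share may be small.** Criterion 5 looks back one month, whereas the severity index covers three months and the parasuicide count a lifetime (Outcomes). A patient negative for one month may have shown the behaviour shortly before. At f = 5% the diluted power is 0.83, and at 10% it is 0.79, close to nominal.
- **A zero effect in the f group is assumed.** If, for illustration, that group showed 40% vs 13%, power at f = 20% would be 0.82.
- **The comparison is not biased.** Level of self-harm (parasuicide count of 14 or more) is a minimization variable, so the risk is lost power.
- **The Discussion does not report a benefit only in patients with high baseline levels.** It says that positive effects were found in them.

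A reader might also infer that the primary analysis should move to patients with the behaviour at baseline. At f = 30% that subset (about 17 per arm) has power 0.70 against 0.60 for the diluted whole. But it still misses 0.80, gains nothing at f = 10% (0.79 either way), and gives up the comparison of all randomised patients that the plan rightly makes primary.

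None of this removes the conflict between the eligibility text and the Discussion, or the silence on which population the rates describe.

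**Conclusion.** The concern holds as an inconsistency and an unstated assumption; an error in the sample size is not shown. The Abstract, Participants and Inclusion criteria admit patients without recent parasuicidal behaviour, and the Discussion says the programme was restricted to patients with it. Both cannot describe the intake.

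The consequence for power is conditional. If the rates refer to the mixed population, the stated power stands. If they refer to patients with the behaviour, the loss is negligible up to about 10% without it and material from about 20% (0.70, falling to 0.49 at 40%). This rests on assumed shares, on no treatment effect in patients without the behaviour, and on about 25 analysed per arm.

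**What to change.** 1. Reconcile the Abstract, Participants and Inclusion criteria with the Discussion, so that one intake is described. Which intake is meant is for the sponsor to say.
2. State the population to which 60% and 20% refer, and how a patient without the behaviour at entry is scored on an endpoint worded as 'still' showing it.
3. Keep all randomised patients as the primary analysis. Add baseline parasuicidal status (yes/no, with a stated look-back window) as a covariate in the longitudinal logistic regression, and do not also use the baseline assessment as an outcome in that model. The parasuicide count and the severity index already collect it before randomisation.
4. Pre-specify the comparison in patients with the behaviour at baseline as a secondary analysis.
5. Restate the power for the share actually enrolled. The article gives the trial as still recruiting, so this can be settled before outcomes are analysed.

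The cost is slight: a little more analysis and possibly a less favourable power figure. Adjustment should not be expected to restore the lost power, as its gain in the scenarios considered is about 0 to 7 percentage points. Its value lies mainly in making the estimate interpretable in a mixed sample.

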### Exclusion criteria

1) IQ < 80

2) Chronic psychotic condition

3) Bipolar disorder

4) Hard drug abuse that requires inpatient detoxification

5) Forced treatment framework

6) Started DBT in the year preceding intake

7) Repeatedly fails to return the screening instrument or does not attend for a thorough examination

8) Disagrees with outcome of randomization

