### Implementation

When patients register in the participating psychiatric centers, crisis team members or staff members working at the front office decide whether or not this patient is a candidate for DBT, based on a rapid assessment of BPD symptomatology. Patients are informed about the central recruitment and diagnostic facility and are given the phone numbers of the project leader and coordinator. After a short, standardized telephone interview with the project leader or the coordinator, in which general information on the interventions and study is given, patients need to fill out a screening instrument (Vragenlijst Kenmerken Persoonlijkheid, VKP) [26] and send it back to the central diagnostic facility. Subsequently, a psychologist contacts the patient for a briefing of the results. If the screening instrument indicates that presence of BPD is probable, then psychologist and patient make an appointment for a thorough examination within three weeks. During this thorough examination, with use of the MINI-PLUS and SCID-II, presence of DSM axis I and axis II disorders are verified. Frequency of borderline complaints and parasuicidal gestures are assessed using respectively BPDSI and LPC. All assessment tools employed have demonstrated reliability and validity (described in detail below). Informed consent is discussed and signed. After signing the informed consent, patients are randomized and the diagnostician reports the allocation of the treatment back to the patients. The allocated treatment center then contacts the patient and starts treatment.

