### Blinding

No blinding took place.

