### Statistical analysis

All participants who are randomised will be included in the comparison and analyzed according to their randomized allocation (intent-to-treat analysis). Wherever possible, we will continue to collect follow-up data from participants after they drop out of treatment, so that the dataset will be as complete as possible. All analyses will be carried out using SPSS (Statistical Package for the Social Sciences) 19 [53]. The effect of the intervention in terms of proportion of respondents still showing suicidal and/or self-destructive behavior after 12 weeks, and the retention of this effect between 24, 36 and 52 weeks, will be computed with the help of longitudinal logistic regression, with time, experimental condition and their interaction as independent variables. The effect of the intervention in terms of reduction in mean BPDSI, LPC, SF-36, and the BSI ratings over time, will be computed with the help of a mixed model linear regression analysis with time, experimental condition and their interaction as independent variables. Missing values will be taken into account by using full information maximum likelihood method estimation. Since there may be some heterogeneity in the implementation of standard DBT across the three different regional centers, between-center heterogeneity will be explored in subgroup analyses.

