However, problems can be expected as a result of the randomization. The fact that allocation of setting is random (outpatient versus inpatient) will create an important toll for participants, because they may be randomized to a treatment condition that was not their primary choice. This involves acceptance of uncertainty. Furthermore, allocation to the experimental program involves an inpatient setting for 12 weeks, which may be difficult to organize for patients with families and work.

Another important problem results from the fact that although an independent, central diagnostic facility was created, the study has no influence on the speed with which patients enter the treatment conditions. The outpatient DBT teams that are part of the trial have a limited capacity and as a result usually have waiting lists.

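### Exclusion criterion 8 can only be met once the patient knows the allocated arm, so it contradicts the intent-to-treat rule; if applied, it removes the protection of randomisation

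*Protocol article*

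**What the plan says.** In the protocol article, the last item under Exclusion criteria is "Disagrees with outcome of randomization". The last item under Inclusion criteria is a separate condition: "Understands and agrees with randomization procedure".

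The Implementation section fixes the order of events: "After signing the informed consent, patients are randomized and the diagnostician reports the allocation of the treatment back to the patients". The Blinding section reads "No blinding took place".

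The Statistical analysis section states: "All participants who are randomised will be included in the comparison and analyzed according to their randomized allocation (intent-to-treat analysis". It adds that, wherever possible, "we will continue to collect follow-up data from participants after they drop out of treatment".

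The Discussion foresees difficulty with allocation. Of the participants it says that "they may be randomized to a treatment condition that was not their primary choice", and of the 12-week inpatient stay, "which may be difficult to organize for patients with families and work".

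**The concern.** An eligibility criterion should be settled before randomisation. This one cannot be, because a patient can disagree with an outcome only after hearing it. The same patient is then excluded by the eligibility list and included by the analysis rule, and the article does not say which prevails.

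If the criterion is followed, patients leave each arm for reasons connected with the arm they drew. Those who would object to 12 weeks of admission need not resemble those who would object to outpatient care. The groups that remain could then differ in baseline risk of self-harm, and balance on the minimisation factors (borderline severity, level of self-harm, age) could be disturbed. This bears directly on the primary comparison, the proportion still showing suicidal or self-harming behaviour at 12 weeks.

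**Working it through.** **1. When can the criterion be met?** By the Implementation section the order is consent, randomisation, disclosure of the arm. Disagreement with the outcome can arise only after the third step. With no blinding, the patient then knows the arm.

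**2. Is it a restatement of inclusion criterion 8?** No. Inclusion criterion 8 concerns the procedure and can be assessed before randomisation. Exclusion criterion 8 concerns the outcome.

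**3. Can both rules be followed?** Take a patient who is randomised, learns the arm and objects. The Exclusion criteria remove this patient; the Statistical analysis section retains the patient in the allocated arm. Both cannot hold.

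**4. The plan's own figures.** The Sample size section gives 20% versus 60% at 12 weeks, power 0.80, α = 0.05, 23 per arm, about 70 in total with 30% drop-out. A two-sided comparison of two proportions without continuity correction gives 23 per arm. Then 23 / 0.70 = 32.9, so 33 per arm and 66 in total, consistent with about 70. The sample size is not in question here.

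**5. How large could the bias be?** The article gives no refusal rate and no refuser risk, so the following are assumptions: true event rate 60% in both arms (no treatment effect), a share r of each arm excluded, and risk q among those excluded. The retained rate is

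(0.60 − r·q) / (1 − r)

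| r | q outpatient | q inpatient | Retained outpatient | Retained inpatient | Spurious difference |
|---|---|---|---|---|---|
| 0.10 | 0.60 | 0.60 | 60.0% | 60.0% | 0 |
| 0.20 | 0.60 | 0.60 | 60.0% | 60.0% | 0 |
| 0.10 | 0.70 | 0.50 | 58.9% | 61.1% | 2.2 points |
| 0.20 | 0.70 | 0.50 | 57.5% | 62.5% | 5.0 points |
| 0.10 | 0.90 | 0.30 | 56.7% | 63.3% | 6.7 points |
| 0.20 | 0.90 | 0.30 | 52.5% | 67.5% | 15.0 points |

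Example, third row: (0.60 − 0.10 × 0.70) / 0.90 = 0.53 / 0.90 = 58.9%. As laid out, the bias runs against the inpatient program; exchanging the two values of q gives the same size in its favour. The difference is also zero whenever exclusion shifts both arms equally. With about 35 patients per arm, four exclusions (4 / 35 = 11%) already exceed the 10% row.

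**6. Effect of retaining decliners.** Assume that inpatient decliners keep the 60% control risk. With 10% declining, the inpatient rate is 0.90 × 20% + 0.10 × 60% = 24%, so the difference falls from 40 to 36 points. With 20% declining it is 0.80 × 20% + 0.20 × 60% = 28%, a difference of 32 points. At 24.5 analysed per arm (35 × 0.70), power falls from 0.84 to 0.74 and 0.62. If all 35 per arm supply outcomes, it falls from 0.94 to 0.88 and 0.78.

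**7. Effect of excluding them instead.** If exclusions in one arm come on top of the 30% drop-out and the 40-point effect is otherwise unchanged, power is 0.81 at 10% and 0.79 at 20%. Exclusion therefore costs less power under these assumptions, but at the price of a comparison that may be biased.

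**The case against.** The strongest reply is that the analysis rule is already right. If the Statistical analysis section governs, nobody leaves the comparison and no bias arises. The article nowhere says that patients meeting criterion 8 are dropped from the analysis set, and the allocation mechanism (minimisation with a biased coin) is untouched either way. This stands to the extent that the harm is conditional on criterion 8 being applied. It does not remove the contradiction.

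A second reply is that the criterion is a loosely worded screening condition, meaning unwillingness to accept either arm. The other seven exclusions can indeed be judged before randomisation. But inclusion criterion 8 already covers that condition, and the wording refers to the outcome.

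Two stronger readings are tempting and not supported. A reader might infer that the plan itself expects refusal to differ by arm. It does not say so: the Discussion mentions non-preferred allocation and the difficulty of arranging an inpatient stay, and the Participants section predicts only where referrals will come from. Arm-dependent refusal is a reasonable inference from these remarks and no more. A reader might also take 7 to 15 points as the expected bias. Those figures need opposed and extreme refuser risks in the two arms; milder assumptions give 2 to 5 points, and average-risk refusers give none.

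Finally, retaining decliners has a real price in a trial of 70, and a patient who withdraws from the research cannot be kept in follow-up. Both points stand and are reflected in the fix.

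**Conclusion.** The point holds as a contradiction between the Exclusion criteria and the Statistical analysis section, and it should be corrected. It rests only on the article's stated sequence and wording.

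The consequence is conditional: if criterion 8 is applied, the retained groups lose the protection of randomisation. It does not follow that the comparison is already biased. On the assumptions shown (60% true rate in both arms, 10% to 20% refusal in each), the spurious difference ranges from 0 to 15 points in either direction, against a planned effect of 40 points. The documents do not allow a narrower statement.

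**What to change.** - Delete exclusion criterion 8. Keep inclusion criterion 8 and state that it is assessed before randomisation.
- State that a patient who declines the allocated treatment stays in the intent-to-treat set in the allocated arm, is invited to all assessments subject to the right to stop at any time (Ethical precautions and crisis management), and is reported as a refusal by arm in the flow chart. A patient who also withdraws from the research is counted as randomised, with outcomes missing from that point.
- Restore to the intent-to-treat set any patient already excluded under this rule. The article gives the trial status as recruiting, so this can still be put in place for later patients.

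The cost is a short amendment, follow-up invitations to decliners, and dilution of the effect by non-adherence: for example from 40 to 36 points, with power falling from 0.84 to 0.74 at 24.5 analysed per arm, if 10% of the inpatient arm decline and keep the control risk (assumption). That dilution belongs to the intent-to-treat analysis the plan has already chosen. Obtaining outcomes from decliners and drop-outs would recover part of the lost power.
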